**Figure 1 F1:**
[figure not shown]
Flow chart of study design (Consolidated Standards of Reporting Trials diagram). All outcome and process measures will be completed at all time points. MemFlex, Memory Flexibility training.

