#### Statistical analysis plan

The trial statistician is blind to study objectives, and will complete all analyses in accordance with CONSORT standards. No interim analyses are planned during data collection. Between-group difference on our primary clinical outcome of number of depression-free days will be analysed using an independent samples t-test, or analysis of covariance if necessary to account for any baseline differences. Time to depressive relapse will be compared between groups using Cox regression survival analysis. Analysis of our cognitive target variable, secondary clinical outcomes and additional process measures will be analysed using analysis of variance (ANOVA) with time (pre, post, 6 and 12 follow-up) as a within-subjects factor, and condition (MemFlex, psychoeducation) as a between subjects factor. Any baseline differences in the cognitive target, symptom severity on the BDI-II, concurrent treatment or demographics will be covaried in analyses. Diagnostic status at 12-month follow-up will analysed using logistic regression. Residual depression symptoms and number of previous episodes (as an index of depression severity), and score on the AMT-AI (as an index of bias severity) at preintervention will be explored as moderators of treatment efficacy by computing product variables that will be analysed using linear regression. Finally, we will explore mechanisms of change by determining whether intervention effects are mediated by change on the AMT-AI and the other process measures. Indirect effects will be analysed using bootstrapped samples in the Process statistical package. Intent-to-treat analysis will be used for those lost to attrition by using multiple imputation to account for missing data. The number of imputed datasets will approximate the percentage of missing data.^46^ Any exploratory, per-protocol analyses will use data from participants who have completed six out of the eight workbook sessions. Exploratory ANOVAs will also be completed to explore between-group difference in pre-to-post intervention change on the separate AMT-AI blocks, to determine whether MemFlex may have a larger impact on specific, categoric or alternating recall.

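### Depression-free days is covariate-adjusted only if a baseline difference is seen, with no criterion for a difference, so chance picks the model and most of the precision in collected baselines is lost

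*Protocol article*

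**What the plan says.** Under Statistical analysis plan, the protocol article says the primary outcome of depression-free days "will be analysed using an independent samples t-test, or analysis of covariance if necessary to account for any baseline differences". A later sentence extends the idea to the other analyses: "Any baseline differences in the cognitive target, symptom severity on the BDI-II, concurrent treatment or demographics will be covaried in analyses". Neither sentence defines a difference, by test, threshold or standardised size.

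For the second primary outcome, "Time to depressive relapse will be compared between groups using Cox regression survival analysis"; no covariate is named. The cognitive target, secondary outcomes and process measures use "analysis of variance (ANOVA) with time (pre, post, 6 and 12 follow-up) as a within-subjects factor", and 12-month diagnostic status uses logistic regression.

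The relevant baselines are collected. The legend to Figure 1 states: "All outcome and process measures will be completed at all time points", which covers the BDI-II and the AMT-AI. The moderator analysis names "Residual depression symptoms and number of previous episodes (as an index of depression severity), and score on the AMT-AI (as an index of bias severity"), all measured before the intervention, so number of previous episodes is also on file. These variables enter unconditionally only in that exploratory analysis. Number of previous episodes is not on the list of variables to be covaried, although the open wording for depression-free days could let it in if it happened to differ.

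**The concern.** Whether a variable is imbalanced and whether it predicts outcome are separate questions, and only the second determines whether adjustment improves the estimate. A rule triggered by imbalance can bring in variables unrelated to relapse and leave out prognostic ones that happen to be balanced. Because no criterion is given, the choice between t-test and ANCOVA stays open until the arms have been compared.

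This matters because the Power analysis section describes an exploratory trial meant to yield a range of likely effect sizes for planning a later one, with about 25 evaluable participants per arm. Precision of the estimate is the main product, and an analysis that discards it weakens what the later trial will be planned on.

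The rule also sits badly with the repeated-measures ANOVAs. There the pre score is already a level of the time factor, so covarying a baseline AMT-AI or BDI-II difference would use the same score as both outcome and covariate.

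**Working it through.** **Sample size.** The plan states 25 per arm after up to 25% attrition, and 35 recruited. 25 / 0.75 = 33.3, so 34; and 35 × 0.75 = 26.25, which is at least 25. The stated figure holds. No alpha, power, effect size or SD is given, so there is no power figure to reproduce.

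**Assumptions, none from the document.** R² between baseline covariates and depression-free days of 0.05 to 0.40; imbalance declared at p < 0.05; a normally distributed outcome; illustrative d = 0.5 where power is quoted.

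**Closed form: t-test against fixed ANCOVA with one covariate.** The 95% half-width in SD units is t × √(2/n) for the t-test and t × √[(2/n)(1 − R²)(1 + 1/(2n − 4))] for ANCOVA.

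| n per arm | t-test | R² = 0.10 | R² = 0.25 | R² = 0.40 |
|---|---|---|---|---|
| 25 | 0.57 | 0.55 | 0.50 | 0.45 |
| 35 | 0.48 | 0.46 | 0.42 | 0.37 |

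**Simulation: stated rule against fixed ANCOVA, 25 per arm, one covariate, 20,000 null trials.** The gain is the squared ratio of the two SDs, minus 1.

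| R² | SD, t-test | SD, stated rule | SD, fixed ANCOVA | Gain over stated rule |
|---|---|---|---|---|
| 0.10 | 0.2837 | 0.2806 | 0.2719 | (0.2806/0.2719)² − 1 = 6.5% |
| 0.25 | 0.2809 | 0.2720 | 0.2461 | (0.2720/0.2461)² − 1 = 22% |
| 0.40 | 0.2820 | 0.2667 | 0.2199 | (0.2667/0.2199)² − 1 = 47% |

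At R² = 0.25 the rule recovers (0.2809² − 0.2720²) / (0.2809² − 0.2461²) = 0.0049 / 0.0183, about 27% of the available variance reduction. Power at d = 0.5 is 0.41 for the t-test, 0.41 for the rule and 0.50 for fixed ANCOVA.

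**35 per arm, one prognostic covariate among five candidates, R² = 0.25, 6,000 trials.** SD is 0.232 under the rule and 0.206 fixed: (0.232/0.206)² − 1 = 27%.

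**Sensitivity.**
- R² = 0.10: runs with one to three fixed covariates gave gains of about 5–10%. The shortcut 1/(1 − 0.10) = 1.11 overstates this, because it compares with the plain t-test and ignores the degrees of freedom spent.
- R² = 0.05, three covariates, 25 per arm: variance ratio 0.999, so no gain.
- Total R² spread over four covariates, all fitted, 25 per arm: (0.2845/0.2819)² − 1 = 2% at R² = 0.10 and (0.2775/0.2553)² − 1 = 18% at R² = 0.25. The set should be small.
- Imbalance threshold of 20% rather than 5%, R² = 0.25: the gain falls to about 15–16%.

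**How often chance changes the model.** With independent candidates tested at 5%, the probability that at least one is flagged is 1 − 0.95⁴ = 18.5% for four, 1 − 0.95⁵ = 23% for five and 1 − 0.95⁷ = 30% for seven. With four tested at 10% it is 1 − 0.90⁴ = 34%.

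**Type I error.** Under a strict 5% imbalance rule it was 0.040 to 0.050, so not inflated.

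**The case against.** The best defence is that the loss is unproven. The document gives no R², and participants must be in partial or full remission, so baseline BDI-II may have a restricted range and predict little. The 5% test is also assumed. Depression-free days is bounded by follow-up and may be skewed, which the normal model does not capture. The trial makes no power claim, so power at d = 0.5 is only illustrative. All of this stands, and it is why the size is given as a range reaching down to nil.

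Scope is limited too. The ANOVAs already use every participant's pre score through the time factor. In the Cox and logistic models, adjustment does not shrink the standard error of the log HR or log OR; it changes the estimand to a conditional effect, and the benefit is mainly power and a fixed model. A reader might infer that the same precision is lost in every analysis. The calculation supports that only for depression-free days.

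A reader might also infer bias or excess false positives, because the statistician who runs the analyses also produced the allocation. The document does not support this. The statistician is described as unaware of the study's objectives, the trigger is baseline data rather than outcomes, and a strict rule does not raise type I error. A rate of about 0.07 to 0.08 would arise only if the more favourable of t-test and ANCOVA were reported, and nothing in the text says that would happen.

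Finally, a separate analysis plan might name covariates. But the article does not leave the matter open: it states a data-dependent rule, which such a plan would have to replace.

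**Conclusion.** The point holds for the primary analysis of depression-free days. The covariate rule is data-dependent, has no criterion, and selects on imbalance rather than prognostic value. Under an assumed 5% imbalance test, fixed adjustment is worth roughly 5–10% more participants than the stated rule at R² = 0.10 and about 22–27% at R² = 0.25; it is near nil at R² = 0.05 and smaller if the threshold is looser. Confidence is high that the rule is badly fixed and low on the exact size. This is a matter of efficiency and of a model that varies by chance, not of bias or false positives. It should be changed, but it does not invalidate the trial.

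**What to change.** Delete both baseline-difference sentences and replace them as follows.

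- **Depression-free days:** ANCOVA with baseline BDI-II and number of previous episodes, included regardless of observed balance; report the unadjusted estimate alongside.
- **Time to relapse:** Cox regression with the same two covariates, stating that the HR is conditional on them.
- **12-month diagnostic status:** the same set in the logistic model if event numbers allow, with the OR likewise described as conditional. The document gives no relapse rate, so this cannot be settled now.
- **Repeated-measures ANOVAs:** do not also covary an outcome's own pre score where it is already a level of the time factor.

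The cost is wording, two degrees of freedom, and HRs and ORs that are conditional effects. Both covariates are already collected, and the article's Ethics and dissemination section provides for amendments to be published with the trial results.

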#### Primary clinical outcomes

The primary clinical outcomes are number of depression-free days from postintervention to 12-month follow-up, and number of days until depressive relapse, both according to the LIFE.

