#### Additional process measures

We have previous evidence to suggest that MemFlex will impact rumination, social problem solving and cognitive avoidance in samples remitted from depression.^34^ We will therefore assess whether these factors may mediate the impact of MemFlex on our primary and secondary outcomes. Rumination will be measured using the Rumination Response Scale,^41^ cognitive avoidance will be measured using the Cognitive Avoidance Questionnaire^42^ and social problem solving will be indexed on the short version of the Means-Ends Problem-Solving (MEPS) task.^43^ We will also assess verbal fluency using the Verbal Fluency Task^44^ to determine whether the programme impacts the fluent retrieval of verbal information. Each of these measures possesses adequate psychometric properties and has been previously used in evaluation of autobiographical memory interventions.^7 34 35^ Parallel forms of these measures will be counterbalanced and administered at all time points.

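### The only methods named for moderators (linear regression) and mediation (bootstrap in Process) do not suit censored time to relapse; exploratory analyses only

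*Protocol article*

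**What the plan says.** All of this is in the protocol article.

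- **Primary clinical outcomes.** There are two, both from the LIFE interview: "number of depression-free days from postintervention to 12-month follow-up" and "number of days until depressive relapse, both according to the LIFE".
- **Statistical analysis plan, main analyses.** "Time to depressive relapse will be compared between groups using Cox regression survival analysis". Depression-free days get a t-test or analysis of covariance, and 12-month diagnostic status gets logistic regression.
- **Statistical analysis plan, moderators.** Residual symptoms, number of previous episodes and baseline AMT-AI score are to be explored as moderators of efficacy "by computing product variables that will be analysed using linear regression". The sentence does not say which outcome measures efficacy.
- **Additional process measures.** The aim is to "assess whether these factors may mediate the impact of MemFlex on our primary and secondary outcomes". This takes in days until relapse.
- **Statistical analysis plan, mediation.** "Indirect effects will be analysed using bootstrapped samples in the Process statistical package". No survival model is mentioned.

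**The concern.** Days until relapse is not a fully observed number. For a participant still well at 12 months, or lost earlier, only a lower bound is known. The plan respects this in its main comparison by using Cox regression, but the methods named for moderators and mediation carry no such provision.

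An analyst who follows the text must put some number in the outcome column for each censored participant, and the moderator or indirect effect then depends on that choice. Even with a defensible choice, a product term in days answers a different question from an interaction on the hazard scale, so the moderator result need not agree with the Cox result it is meant to explain. Binary 12-month status has a similar mismatch if its moderators are tested by linear regression.

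At stake is the evidence on for whom and how MemFlex works. The Discussion names exploring mechanisms as an aim, and the results are to inform a later trial.

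**Working it through.** **The plan's own figures.** The article gives no relapse rate, hazard ratio or moderator effect, so there is no figure on this point to reproduce. The one input taken from it is attrition of up to 25% (Power analysis). That section is consistent: 25/(1 − 0.25) = 33.3, so 34 per arm are needed and 35 are planned.

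**Assumptions, none from the document.** Relapse times are exponential. Control 12-month relapse risk r at the average moderator value is 30%, 50% or 70%. The treatment hazard ratio (HR) is 0.5 or 0.7. The moderator multiplies the hazard by 1.5 per SD. There is no treatment-by-moderator interaction on the log-hazard scale. Dropout is 25%, uniform over the year and unrelated to outcome.

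**Step 1: hand check at r = 50%, HR = 0.5.** Write Λ for the cumulative hazard over 365 days. Mean relapse-free days within the year are 365 × (1 − e^−Λ)/Λ.

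- Average moderator, control: Λ = −ln(0.5) = 0.693, giving 263.3 days.
- Average moderator, MemFlex: Λ = 0.347, giving 308.5 days. Difference 45.2 days.
- Moderator +1 SD: Λ = 1.040 and 0.520, giving 226.9 and 284.6 days. Difference 57.7.
- Moderator −1 SD: Λ = 0.462 and 0.231, giving 292.3 and 325.9 days. Difference 33.6.

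The hazard ratio is 0.5 at every moderator value, yet the difference in days rises by about (57.7 − 33.6)/2 = 12 days per SD. The linear product term picks this up purely because of the scale.

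**Step 2: effect of coding dropout as relapse.** For modest hazards the difference in days grows roughly with the square of follow-up time. Averaged over uniform dropout times it is therefore about one third of the full-year difference. The overall difference becomes about 0.75 + 0.25 × 1/3 = 0.83 of its full value, a loss of about 17%.

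**Step 3: large-sample simulation** (400,000 participants; Cox fitted on 20,000). The first differences column has everyone followed to day 365. The second has dropout dates taken as relapse dates.

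| r | HR | Censored, any cause | Difference in days, full | Dropout as relapse | Change | Linear product term, full | Cox interaction (log scale) |
|---|---|---|---|---|---|---|---|
| 30% | 0.5 | 79% | 28.3 | 24.1 | −15% | 9.1 | −0.019 |
| 30% | 0.7 | 76% | 16.7 | 13.8 | −17% | 5.1 | −0.007 |
| 50% | 0.5 | 64% | 45.3 | 38.1 | −16% | 10.9 | 0.039 |
| 50% | 0.7 | 60% | 26.1 | 21.7 | −17% | 6.0 | 0.002 |
| 70% | 0.5 | 48% | 60.5 | 51.1 | −15% | 9.9 | −0.001 |
| 70% | 0.7 | 43% | 33.3 | 28.2 | −15% | 4.6 | 0.006 |

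The Cox model with the product term recovers the treatment effect (0.49-0.50 for a true 0.5; 0.68-0.71 for a true 0.7) and an interaction near its true value of zero. With dropout coded as relapse, the linear product term also moves, to between 4.1 and 9.2 days per SD. Entering only those who relapsed would cut the difference further (45.3 to 11.6 days at r = 50%, HR 0.5), but the plan does not propose that.

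**Not computed.** No indirect effect was simulated. The mediation part rests on setting the sections side by side: the stated scope includes a censored outcome, and the stated method includes no survival model.

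**The case against.** The strongest reply is that the plan never says relapse time is treated as fully observed. The moderator sentence names no outcome. Since the same section assigns Cox to relapse time and logistic regression to status, linear regression may be meant for depression-free days alone. That reading is possible but nowhere stated, and the Introduction frames the expected benefit in terms of both primary outcomes. It does not rescue mediation, whose scope expressly covers primary and secondary outcomes.

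A second reply is that a linear model on days truncated at day 365 is a valid analysis of the difference in restricted mean days. This is right when follow-up is complete. What remains then is a difference of scale from the Cox analysis, not a bias; bias enters through dropout.

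A third reply is that these analyses are exploratory and do not feed the primary estimates. This stands and limits the severity.

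A reader might also infer more than the article supports:

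- **That the primary effect on relapse is wrong.** It is estimated by Cox regression, which handles censoring.
- **That the missing-data rule is an error.** The text is "Intent-to-treat analysis will be used for those lost to attrition by using multiple imputation to account for missing data". It does not say that relapse times are imputed. Imputing scores and depression-free days can coexist with censoring in the Cox model, and a full analysis plan would commonly settle this.
- **That the mediators are wrongly timed.** Process measures are also taken at 6 and 12 months, but the mediation sentence fixes no interval and is compatible with change from pre- to postintervention.

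**Conclusion.** The concern holds in limited form. The stated mediation scope includes right-censored relapse time, while the stated mediation method makes no provision for censoring. The only moderator method named is linear regression, with no exception for relapse time or for binary status. If these methods are applied to days until relapse, the results depend on how censored times are coded and are on a different scale from the plan's Cox analysis.

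Under the assumed scenarios, 43-79% of participants are censored. Coding dropout as relapse costs about 15-17% of the treatment difference in days, and a linear product term of about 5 to 11 days per SD appears where the hazard scale has no interaction. These figures rest on assumed relapse risks, hazard ratios, moderator strength and non-informative dropout. The 15-17% describes a treatment difference from a linear model, not the planned Cox estimate.

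Severity is minor to moderate and confined to the exploratory moderator and mediator analyses. The main relapse comparison is sound.

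**What to change.** - **Name the outcome of each moderator and mediation model.**
- **Moderators.** Test time to relapse with the product term in the Cox model and 12-month status with the product term in the logistic model. Keep linear regression for depression-free days.
- **Mediation.** Limit the bootstrap analysis to outcomes it can handle, such as depression-free days and BDI-II, or specify a survival-based mediation method for time to relapse. Preferably take change from pre- to postintervention as the mediator, so that it precedes the period over which the outcome accrues.

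The cost is a few sentences in the analysis plan and slightly different code, with no new data. The Cox and logistic models are already planned. The downside is that there may be no bootstrap indirect effect for time to relapse; if so, the mediation scope stated under Additional process measures should be narrowed to match.

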Autobiographical memory, that is, memory of personal life experiences, is integral in forming one’s sense of self,^6^ and disruptions in autobiographical memory increase risk of depression (for review see ref^7^). Autobiographical information is stored in a fluid manner, and can therefore be retrieved in a variety of formats, including as specific, single incident events that are rich in detail (eg, when I forgot my purse and couldn’t buy my train ticket), or as generalisations that summarise consistency across a category of events (eg, catching the train to work every day). Memory flexibility refers to the ability to successfully navigate the autobiographical information database to deliberately retrieve memories varying in detail and emotional valence. In depression, flexible movement within the autobiographical information database is compromised,^8 9^ resulting in relative difficulties in retrieving both general and specific memories.^8 10 11^ This can create functional impairment as both types of memory are necessary in daily cognitive skills; for example, specific memories can help to guide problem solving^12^ while general memories encode regularities of experiences that can be used to inform judgements of the self, world and others.^13 14^ Impaired recall of specific memories is a key predictor of the first onset of depression^15^ and also of future depressive episodes in those with a history of recurrent depression (for meta-analysis see ref 16), although comparable studies examining the predictive effects of impaired generality or flexibility have yet to be carried out.

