A core feature of reduced flexibility is the chronic over-retrieval of autobiographical memories that are: (1) negative in emotional valence and (2) overgeneral in nature. Regarding valence, depressive risk is increased by a habitual and inflexible inclination towards negative memories, and subsequently, a neglect for positively valenced and neutrally valenced memories.^17^ However, it is not simply that negative information is retrieved more readily, but that when positive information is recalled, it is less vivid^18^ and therefore has an attenuated impact on affect, reducing the emotional benefits that are gained from recalling positive memories.^19^ In this way, biased memory retrieval can impair the ability to repair transient low mood.^20^ In addition, the absence of vivid, positive memories of oneself and a continual emphasis on negative autobiographical information reinforces the negative self-schemata that maintain and promote depression.^21^

Difficulties in intentional autobiographical retrieval also increases risk for depression. A tendency towards general memory recollection and reduced retrieval of specific memories is evident in those with current depression, however, the overgeneral retrieval style does not remit with depressive symptoms,^11^ suggesting that reduced specific recall is a durable cognitive marker for depression^16^ that may not be shifted by current psychological treatments,^22^ though this has not yet been well explored. Repeated recall of overgeneral summaries may promote depression by reinforcing overly general (negative) attributions regarding the self (eg, I always fail) and the world (eg, the world is an unfair place). Previous research has also demonstrated that impaired retrieval of specific memories impacts a number of intermediate factors that promote depression. Abstract and overgeneral memory recall intensifies rumination,^23^ which in turn creates negative affect, impairs mood regulation, and is itself a risk factor for recurrent depression.^24^ Impaired retrieval of specific memories also reduces the ability to establish intimacy in social communication,^25^ impairs problem solving^26^ and limits the ability to appropriately restrain the overly general, negative self-judgements that are characteristic of depression.^27^

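### Change scores are the mediators, but baseline is covaried only if the arms differ; each mediator's baseline score should be in both mediation equations regardless

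*Protocol article*

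**What the plan says.** The Statistical analysis plan section of the Protocol article sets out the mediation analysis in two sentences. The first says "we will explore mechanisms of change by determining whether intervention effects are mediated by change on the AMT-AI and the other process measures". The second adds "Indirect effects will be analysed using bootstrapped samples in the Process statistical package". The Additional process measures section names rumination, social problem solving and cognitive avoidance as candidate mediators and says the trial will "assess whether these factors may mediate the impact of MemFlex on our primary and secondary outcomes".

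No mediation equation is given. The text does not say whether change is raw or residualised, over which visits it is taken, or which covariates the mediation models contain. One general covariate rule appears in the same section: "Any baseline differences in the cognitive target, symptom severity on the BDI-II, concurrent treatment or demographics will be covaried in analyses". Of the mediators, only the cognitive target (the AMT-AI) is named there.

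**The concern.** A change score is the later score minus the baseline score. Within an arm it is usually negatively correlated with baseline, since people who start low tend to gain more. If the baseline score is also related to outcome, it confounds the slope of outcome on change. Randomisation protects the effect of treatment on the mediator, but not the effect of the mediator on outcome. Balance between the arms is beside the point, because the confounding arises within each arm.

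The Introduction gives reason to expect such a relation for some of the measures. It says "Impaired recall of specific memories is a key predictor of the first onset of depression", describes the persistence of poor recall in remission as "suggesting that reduced specific recall is a durable cognitive marker for depression", and calls rumination a risk factor for recurrent depression. A covariate rule triggered by imbalance therefore guards against the wrong problem. At stake is the estimate of how far MemFlex works through its intended target, which the Discussion lists among the things the trial will begin to explore.

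**Working it through.** **The plan's own figures.** No figure is given for mediation. The only reproducible number nearby is the sample size in Power analysis: 25 / (1 - 0.25) = 33.3, so 34 per arm against the stated 35 (70 in total). That is consistent and is not at issue.

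**Model.** T is randomised arm, M0 the baseline mediator, M1 the later mediator, D = M1 - M0, and Y = b·M1 + g·M0 + d·T + error. Scale so that Var(M0) = 1. Within arm, let Var(M1) = v and let r be the pre-post correlation, so that Cov(M0, M1) = c = r·√v. This treats the outcome as linear, as for depression-free days or BDI-II. The values of b, g, v and r are assumptions; the documents give none of them.

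**Slope on change when M0 is left out.**
- Cov(Y, D) = b(v - c) + g(c - 1)
- Var(D) = v + 1 - 2c
- Slope = [b(v - c) + g(c - 1)] / (v + 1 - 2c)

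By randomisation, the effect of T on D has the same expectation with or without M0. The share of the indirect effect recovered is therefore slope / b.

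**Equal variance (v = 1, c = r).** The slope is (b - g)(1 - r) / [2(1 - r)] = (b - g)/2, so the share is (1 - g/b)/2 whatever r is.

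| g (direct baseline effect) | Share recovered | Simulated, truth 0.25 |
|---|---|---|
| g = b | 0% | -0.001 |
| g = 0.5b | 25% | not run |
| g = 0 | 50% | 0.125 |
| g = -0.5b | 75% | 0.187 |
| g = -b | 100% | 0.249 |

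The simulation used n = 70, 6,000 runs per setting, r = 0.5, an effect of T on the mediator of 0.5 and b = 0.5.

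**Unequal variance (g = 0, r = 0.5).** For v = 1.25, c = 0.559 and the share is 0.691/1.132 = 61%. For v = 1.5 it is 70%. For v = 2, c = 0.707 and the share is 1.293/1.586 = 82% (simulated 0.202 of 0.25). For v = 0.5 it is 19%.

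**What the Introduction's premise implies.** If better baseline memory goes with a better outcome, the overall slope of Y on M0 is positive: b·c + g > 0, so g > -b·c. When c < 1, the share is then below (v - c²)/(v + 1 - 2c). That bound is under 100%, because the denominator minus the numerator is (1 - c)². At equal variance it equals (1 - r²)/[2(1 - r)] = (1 + r)/2, which is 65%, 75% and 85% for r = 0.3, 0.5 and 0.7. At v = 2 and r = 0.5 it is 1.5/1.586 = 95%. Under the premise there is always some attenuation, but its size is open.

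**Does the imbalance rule help?** The plan does not say how a baseline difference is judged, so p < 0.05 is assumed. With v = 1 and g = 0, the rule gives 0.132 of 0.25, against 0.125 with no adjustment. With g = b it gives 0.011, against -0.001. It repairs almost nothing.

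**With M0 in both equations.** The simulated indirect effect is 0.249 to 0.251 against 0.25 in all five settings run. Once M0 is in the model, D and M1 give the same mediator slope, so the change score itself does no harm.

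**The case against.** The strongest reply is that the article never says baseline is left out. It is a condensed account, its wording is compatible with residualised change or with a baseline-adjusted model, and a fuller plan may settle the matter. This stands in part: omission is an inference. But the article is not simply silent. It states a covariate rule, makes that rule depend on arm imbalance, and does not name three of the mediators. Followed as written, the rule leaves baseline out of most models.

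A second reply concerns size. A reader might infer that a change-score analysis can never recover more than half of a true indirect effect. The documents do not support that. The limit of one half needs equal pre and post variance and g ≥ 0, whereas the Introduction describes only an overall association, which is compatible with a moderately negative g. The Introduction also says that prediction by impaired generality or flexibility, as distinct from specific recall, has not yet been studied. The premise is therefore firmer for specific recall and rumination than for the AMT-AI as a flexibility measure. All of this stands.

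A third reply is that nothing decisive depends on this analysis. A reader might infer that it would wrongly dismiss memory flexibility and lead the later trial to drop the right target. That goes too far: the trial's main purpose is to estimate effects on relapse, and the section says only "we will explore mechanisms of change". Even the adjusted model would seldom settle the question. Assuming a 0.5 SD effect on the mediator, b = 0.4, r = 0.5 and residual SD 1, its 95% interval excluded zero in only 35% to 51% of simulated trials with 52 to 70 participants. This limits the severity but gives no reason to keep an avoidable bias.

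**Conclusion.** The point holds in a limited form. The plan names change as the mediator and ties baseline adjustment to arm imbalance, which is not the source of the confounding. If raw change is used under that rule, the indirect effect is attenuated whenever a better baseline score goes with a better outcome and the within-arm slope of post on baseline is below 1. The loss is half at equal variance with no direct baseline effect and total when the baseline effect equals the post effect. It is smaller if post variance exceeds baseline variance or the direct baseline effect is negative. If the outcome depends on change alone (g = -b) there is none. No single figure can be attached to this trial, because the documents supply none of the parameters. Severity is low: the analysis is exploratory, and the primary comparisons and the sample size are unaffected.

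**What to change.** Add one sentence to the mediation text: in every mediation model, the baseline score of that mediator is a covariate in both the mediator equation and the outcome equation, whether or not the arms differ at baseline, and this adjusted indirect effect is the main mediation result. The sponsor can keep change as the mediator, and an unadjusted change-score result may be shown as secondary. Nothing here tests the need for further covariates such as baseline BDI-II, and none is asked for.

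The cost is one sentence and one degree of freedom per equation. No new data are needed: the measures are given at all time points, and Participant allocation places the preintervention assessment before the allocation envelope is opened. The Ethics and dissemination section already provides for amendments to be reported with the results.
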